## Abstract

**Background:**

Smokers attend preferentially to cigarettes and other smoking-related cues in the environment, in what is known as an attentional bias. There is evidence that attentional bias may contribute to craving and failure to stop smoking. Attentional retraining procedures have been used in laboratory studies to train smokers to reduce attentional bias, although these procedures have not been applied in smoking cessation programmes. This trial will examine the efficacy of multiple sessions of attentional retraining on attentional bias, craving, and abstinence in smokers attempting cessation.

**Methods/Design:**

This is a double-blind randomised controlled trial. Adult smokers attending a 7-session weekly stop smoking clinic will be randomised to either a modified visual probe task with attentional retraining or placebo training. Training will start 1 week prior to quit day and be given weekly for 5 sessions. Both groups will receive 21 mg transdermal nicotine patches for 8–12 weeks and withdrawal-orientated behavioural support for 7 sessions. Primary outcome measures are the change in attentional bias reaction time and urge to smoke on the Mood and Physical Symptoms Scale at 4 weeks post-quit. Secondary outcome measures include differences in withdrawal, time to first lapse and prolonged abstinence at 4 weeks post-quit, which will be biochemically validated at each clinic visit. Follow-up will take place at 8 weeks, 3 months and 6 months post-quit.

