**Discussion:**

This is the first randomised controlled trial of attentional retraining in smokers attempting cessation. This trial could provide proof of principle for a treatment aimed at a fundamental cause of addiction.

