### Primary trial outcomes

• Measure of attentional bias during assessment trials of the visual probe task, as measured by the difference in median reaction time (ms) taken to respond to probes replacing smoking-related stimuli versus probes replacing neutral stimuli. This will be assessed at 4 weeks post-quit in abstinent and non-abstinent smokers across both trial arms, following recommendations of Shiffman et al. [60].

• Strength of weekly urge to smoke on the MPSS, measured up to 4 weeks post-quit in abstinent and non-abstinent smokers across both trial arms.

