### Power calculation

The sample size is based on the following. In these calculations, we assume that only quitters will continue to attend clinic and that the measures will be analysed primarily in abstinent smokers, as is standard practice with withdrawal phenomena [60].

We assume conservatively that the effect of 5 sessions of AR will be no greater than the effect of a single session. From the findings of the Attwood et al. study [26], to detect a mean reduction of 26 ms (SD = 43 ms) with 80% power and a type 1 error rate of 5%, 42 participants in each group will be required. We revised this calculation to adjust for baseline attentional bias scores. In our pilot study of AR, we found an estimated correlation coefficient of −0.13 between baseline and post-training measurements. Thus, to detect a reduction of 26 ms with the same standard deviation, power and type 1 error stated above, 42 participants are still required in each group. We expect that at least 50% of participants will reach the Russell standard abstinence criteria at 4 weeks, as the NHS services achieve greater than this, providing about 50 abstinent participants in each arm, sufficient to test this hypothesis.

The trial is an exploratory study but is powered to detect differences in urge to smoke. One study on smokers quitting on pharmacotherapy found that the mean change in urge strength between quit day and week 1 was about 0.5 points measured with the MPSS and had a standard deviation of 1.2 [61]. Another study reported that glucose reduced urge strength by 1.0 points, although this was immediately after dosing [62]. In both of these studies, MPSS urge strength was scored 0–5 [42]. We assume that if AR can reduce urge strength by 0.6 points, then 62 participants in each group will be needed to detect this with 80% power and a type 1 error rate of 5%. From the earlier study [61] we used an estimated correlation coefficient of 0.41 between quit day and post-training urge strength to adjust this power calculation. This means that to detect a 0.6 point reduction in urge strength (SD = 1.2) with 80% power and a type 1 error rate of 5%, 53 participants would be required in each group. In the first 4 weeks, when withdrawal is at its height, this implies that about 200 smokers will be needed, assuming that 60% will achieve abstinence in the first 4 weeks.

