### Analysis

• Primary analyses

• Attentional bias scores on the visual probe task will be calculated by subtracting median RTs to probes that replace smoking-related pictures from median RTs to probes that replace neutral pictures, with positive scores indicating a bias towards smoking cues and negative scores indicating a bias towards neutral cues. Median RTs will be used because distributions of mean RTs are often reported as skewed [33,63]; therefore we do not need to set parameters for outlying RTs. Bias scores, as measured at 4 weeks post-quit, will be used to examine AR effects on attentional bias firstly by trial arm and secondly by abstinence status using ANCOVA. An alpha level of 0.05 will be used. These analyses will be performed using PASW Statistics 18 (SPSS, Inc., 2009, Chicago, IL, USA).

• To investigate AR effects on weekly urge to smoke, data will be analysed using a mixed effects regression model with an autoregressive variance-covariance structure, to allow for variations in craving between participants. This will enable all weekly time points to be included and modelled simultaneously. An autoregressive modelling structure takes into consideration that repeated craving measurements taken closer together in time on the same participant are likely to be more highly correlated than measurements that are taken further apart in time [64]. This modelling technique will be used for MPSS composite scores for urge to smoke (MPSS-C). Regression coefficients, p-values and 95% confidence intervals (CI) will be derived from the models. These analyses will be undertaken using Stata 12.0 (StataCorp, 2011, College Station, TX: StataCorp LP).

• Intention-to-treat analyses will be performed to account for people who drop out of treatment.

• Secondary analyses

• Effects of AR on withdrawal will be examined using the same technique stated for urge to smoke analyses, in a mixed effects regression model of composite scores for withdrawal symptoms (MPSS-M). We will control for baseline MPSS-M scores, as is standard for the MPSS [42].

• To determine the proportion of people achieving abstinence by trial arm, risk ratios (RRs) will be calculated with corresponding 95% CIs. Those reported as lost-to-follow up will be counted as non-abstinent, as is standard in the reporting of smoking cessation trials [39,65].

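### Two primary outcomes are each planned at 5% with no stated rule for combining them; if either one counts as success, the chance of a false positive primary result is about 9–10%

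*Protocol article*

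**What the plan says.** The abstract states: "Primary outcome measures are the change in attentional bias reaction time and urge to smoke on the Mood and Physical Symptoms Scale at 4 weeks" after quit day. The Primary trial outcomes section lists the same two as separate items. The first is "Measure of attentional bias during assessment trials of the visual probe task", assessed at 4 weeks. The second is "Strength of weekly urge to smoke on the MPSS, measured up to 4 weeks post-quit in abstinent and non-abstinent smokers across both trial arms".

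The Power calculation section treats them one at a time. For bias the sample is set "to detect a mean reduction of 26 ms (SD = 43 ms) with 80% power and a type 1 error rate of 5%, 42 participants in" (the figure is per arm), and it stays at 42 after adjustment for baseline. For urge it is 62 per group, or 53 after adjustment, again at 80% power and 5% type 1 error. The same section says: "The trial is an exploratory study but is powered to detect differences in urge to smoke".

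In the Analysis section, the paragraph on attentional bias states: "An alpha level of 0.05 will be used". For the urge model it states: "Regression coefficients, p-values and 95% confidence intervals (CI) will be derived from the models". Nowhere does the article say in what order the two are tested, whether one or both must be positive, or how the 5% is shared.

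**The concern.** With two primary outcomes and no combining rule, the reader cannot tell what counts as a positive trial. There are two natural readings. If either result is enough, the trial has two chances of a false positive primary finding. If both are needed, the power to succeed is lower than the 80% planned for each. Under neither reading do 5% error and 80% power both describe the trial's primary conclusion.

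The choice also affects interpretation, because the two outcomes support different claims. A change in bias without lower urge shows that the task altered task performance. Lower urge without a change in bias does not support the mechanism set out in the aims, where diverting attention from cues is expected to reduce craving. If the rule is fixed only after the results are known, emphasis could fall on whichever outcome is positive.

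**Working it through.** **Inputs from the Power calculation section.**
- Bias: difference 26 ms, SD 43 ms, baseline correlation −0.13, about 50 abstinent per arm (50% of 100).
- Urge: difference 0.6, SD 1.2, baseline correlation 0.41, about 60 abstinent per arm (60% of 100).
- Alpha 5% and power 80% for each. Two-sided testing is stated only for the abstinence calculation, but it also reproduces the sizes below.

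**Assumption.** The article gives no correlation between the two test statistics. The Background describes the link between bias and craving as fairly weak, so 0 to 0.5 is used as the main range.

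**Step 1: reproduce the plan's sizes.** n per group = 2 × [SD × (1.96 + 0.842) / difference]² × (1 − r²).
- Bias: 42.9 unadjusted, × (1 − 0.0169) = 42.2 (stated 42 and 42).
- Urge: 62.8 unadjusted, × (1 − 0.1681) = 52.2, rounded up to 53 (stated 62 and 53).

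All agree within one participant at a full 5% for each outcome. At 2.5% each, the adjusted sizes would be 51.1 and 63.3, that is 52 and 64, so the planning did not use an alpha split.

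**Step 2: error if either result counts.** With independent tests, 1 − 0.95² = 0.0975. With correlated statistics (bivariate normal, critical value 1.96):

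| Correlation | At least one false positive |
|---|---|
| 0 | 9.75% |
| 0.2 | 9.6% |
| 0.5 | 9.1% |
| 0.8 | 7.8% |
| 0.9 | 7.0% |

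The upper bound is 5% + 5% = 10%.

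**Step 3: power if both must be significant.** With 80% on each, joint power is 0.8 × 0.8 = 64% at correlation 0 and 69% at 0.5.

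**Step 4: cost of a rule at the planned numbers.** Power = Φ(difference / [SD × √(1 − r²) × √(2/n)] − critical value), with critical value 1.96 at 5% and 2.24 at 2.5%.
- Bias, n = 50: Φ(3.05 − 1.96) = 86%; at 2.5%, Φ(3.05 − 2.24) = 79%.
- Urge, n = 60: Φ(3.00 − 1.96) = 85%; at 2.5%, Φ(3.00 − 2.24) = 78%.
- Holm rejects an outcome at 2.5%, or at 5% once the other is rejected at 2.5%. At correlation 0, bias is 0.790 + (0.862 − 0.790) × 0.777 = 0.846 and urge is 0.777 + (0.851 − 0.777) × 0.790 = 0.836. At 0.5 they are about 0.836 and 0.826.

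| Rule | Bias (50 per arm) | Urge (60 per arm) |
|---|---|---|
| None (each at 5%) | 86% | 85% |
| Holm | about 84% | about 83% |
| Even split, 2.5% each | 79% | 78% |
| Fixed sequence, bias first | 86% | 73–77% |

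The last figure is the chance that both are significant: 0.862 × 0.851 = 73% at correlation 0, and 77% at 0.5. If only 50 per arm are abstinent for urge as well, urge power is 78% unadjusted and about 76% under Holm.

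**The case against.** A reader might infer that the protocol misstates its error rate. It does not. Each 5% is given for one calculation or one analysis and is correct there; no trial-wise 5% is claimed. The 9–10% also depends on letting either result count as success, and the article does not say that it does.

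The aims pose bias and urge as separate questions. Where each test supports only its own claim, 5% per hypothesis is a recognised position. The trial calls itself exploratory, and the abstract's ambition is modest: "This trial could provide proof of principle for a treatment aimed at a fundamental cause of addiction". A statistical analysis plan, not shown, may supply a rule. A fixed sequence there would not contradict the article, since it too tests each outcome at 0.05.

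Most of this stands, and it limits the size of the point. It does not remove it. Both outcomes carry the primary label with formal power. The aims join them as steps in one argument for one intervention. The exploratory label comes in the same sentence as the claim to be powered for urge, and it does not say which result decides the trial. The point rests on what the article does fix, a full 5% for each of two primaries, and not only on a rule that might appear elsewhere.

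**Conclusion.** The concern holds in a limited form. The plan fixes two primary outcomes at 5% each and leaves their combination open. If either counts as success, the chance of at least one false positive is about 9–10% for correlations between 0 and 0.5, falling to 7.0% at 0.9. These figures assume that neither effect exists, and the correlation is assumed. If both must succeed, the error is at most 5%, but power is 64–69% when each test has 80%, or 73–77% at the planned 50 and 60 per arm.

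A reader might also infer that bias must be tested first because it is clearly the better powered. The document's own assumptions do not show that: at 50 abstinent per arm for bias and 60 for urge, power is 86% and 85%. Bias leads clearly only if 50 per arm is imposed on both. Urge is also the outcome that drives the total of about 200. The choice of order is the sponsor's. The exploratory status makes this something that should be fixed, not a flaw that undermines the trial.

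**What to change.** Before data are seen, state one rule in the Primary trial outcomes section and in the primary analyses that holds the error across the two primaries at 5%. Either of these would do:

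- **Holm across the two.** Test the smaller p-value at 2.5% and, if it is significant, the other at 5%. Neither outcome depends on a chosen order.
- **A fixed sequence, each at 5%,** with the order chosen and justified by the sponsor. If bias comes first, say plainly that a confirmatory claim on urge, the outcome that sets the sample size, becomes conditional on the bias result. If the first test fails, report the second as an estimate with its 95% confidence interval, labelled exploratory.

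The change is to wording only; no extra participants or data are needed. Holm costs about two percentage points of power on each outcome. A bias-first sequence costs bias nothing and urge roughly 8 to 12 points (85% to 77% or 73%). An even split costs about seven points on each and has no advantage over Holm, which is never less powerful.

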**Discussion:**

This is the first randomised controlled trial of attentional retraining in smokers attempting cessation. This trial could provide proof of principle for a treatment aimed at a fundamental cause of addiction.

**Trial registration:**

Current Controlled Trials: ISRCTN54375405.

## Background

Although many people who smoke achieve short-term success with current smoking cessation interventions, the rate of relapse to smoking remains high. Over 75% of initially successful quitters return to smoking within a year, with relapse occurring most commonly in the first 6 months after cessation [1]. At present, there is insufficient evidence to support the use of behavioural methods to prevent relapse in individuals achieving initial abstinence [2]. Most interventions have typically focused on Marlatt and Gordon’s [3] ‘skills’ based approach, which attempts to teach patients to identify situations conducive to relapse and teach cognitive and behavioural coping skills to deal with these situations. However, there is no evidence that the skills based approach diminishes or delays relapse to smoking [4] and so new interventions are required.

More recently, there has been increasing interest in the influence of implicit cognitive processing biases on our understanding of the relapse process [5]. Attentional bias, where drug users show excessive attention towards drug-related cues in the environment, is well-documented in tobacco smokers and users of other drug substances [6,7]. Several theoretical models of attentional bias propose that through repeated drug use, drug-related cues appear appealing to drug users, ‘grab’ attention and become ‘wanted’ to the extent that behaviour is guided towards drug use relatively automatically [8,9]. Further theoretical models propose that increases in attentional bias are both a cause and consequence of high levels of craving [10]. Thus, smokers with high levels of craving may be more likely to search the environment for smoking-related cues, while prolonged attentional processing of smoking-related cues could increase urges to smoke. There is evidence that attentional bias is related to drug craving [11], although this relationship has been reported as somewhat weak [12]. Attentional bias has also been linked to an increase in the likelihood of relapse in smokers [13], alcohol users [14] and heroin addicts [15]. There is also strong anecdotal evidence that environmental and situational cues act as triggers for relapse in abstinent smokers. Control of attentional processes may therefore play a key role in preventing relapse among smokers who are attempting to quit, although current smoking cessation programmes delivered by the National Health Service (NHS) Stop Smoking Services (SSS) in the United Kingdom (UK) do not target attentional biases directly.

Several paradigms measure cognitive processing biases. The most common among these are the visual probe task [16] and Stroop task [17]. In the standard version of the visual probe task, pairs of pictures or words – one drug-related and one neutral stimulus - are presented briefly on a computer screen before a probe appears in the location formerly occupied by one of the pictures or words. Smokers, in comparison to non-smokers, have shown an attentional bias towards smoking by responding faster to probes that appear in the location of smoking-related stimuli rather than neutral stimuli [18,19]. Other drug users have shown an attentional bias towards drug-related stimuli of their choice; for example, cannabis users are faster to respond to cannabis-related stimuli than neutral stimuli [20]. Similarly, the addiction Stroop task has been used extensively to measure selective processing of drug-related stimuli [21]. Processing biases on the Stroop task have been demonstrated in smokers who are typically slower to colour-name smoking-related stimuli than neutral stimuli [22,23].

There is some evidence to suggest that cognitive processing biases are apparent in smokers ever after attempts to stop smoking. The first study to explore this found that ex-smokers, who were enrolled in a smoking cessation programme and had been abstinent from smoking for at least 1 week, had an intermediate bias for smoking-related stimuli, in-between that of smokers and non-smokers [19]. In another study, smokers who were attempting to quit and smokers without such plans had similar levels of attentional bias [24]. In contrast to these studies, two studies found that ex-smokers showed a similar level of processing bias as never-smokers, while smokers exhibited more bias than both other groups [23,25]. In both of these studies, ex-smokers had been abstinent for at least 6 months rather than recently abstinent from smoking. Thus, data are conflicting but it is possible that attentional bias persists early in a quit attempt and resolves with increased duration of abstinence although no study has examined this. However, if attentional bias persists for many months, we might speculate that if there are enduring effects of smoking cues after cessation as suggested in previous research, abstinence could be undermined in initially successful quitters.

Cognitive bias modification (CBM) procedures have been developed in an attempt to change cognitive processing biases using modified versions of the visual probe task and Stroop task [26-33]. CBM procedures are designed to augment or attenuate cognitive processing biases, providing not only a method of studying the causal relationship between attentional bias, craving and relapse, but also a potential treatment for attentional bias in clinical populations. Attentional retraining (AR) is most commonly used in the study of addiction-related attentional bias. Individuals with specific drug use patterns can be trained to increase or decrease attentional bias towards their drug of choice in train-to-attend and train-to-avoid manipulations, respectively [26,28-30,32]. In the train-to-attend manipulation, probes replace drug-related stimuli more frequently than neutral stimuli; by comparison in the train-to-avoid manipulation, probes replace neutral stimuli on a greater number of occasions. Consequently attention is trained towards one particular stimulus type.

Most investigations of AR in addiction have been conducted in laboratory studies of non-treatment seeking alcohol users [28,29,32] and more recently, tobacco smokers [26,30,31]. These studies have typically measured the effects of AR on subjective outcomes, e.g. craving and behavioural outcomes such as drug consumption as well as the change in attentional bias. In the first of these studies comparing a train-to-attend with a train-to-avoid manipulation, training towards alcohol-related stimuli was associated with increases in attentional bias, urge to drink and actual beer consumption. Conversely, training away from alcohol-related stimuli was associated with reductions in attentional bias and beer consumption but not urge to drink. The study was replicated with the inclusion of a control group that received no training towards any particular stimulus type; the predicted direction of change in attentional bias was observed in the groups trained to attend or avoid alcohol-related stimuli, as well as no change in attentional bias in the control group [29]. Alcohol craving increased among participants in the attend group, but only for those who were aware of the experimental contingencies, i.e. participants who reported the relationship between the location of the probe and stimulus-presentation correctly in a post-task questionnaire. However, in contrast to the findings of the earlier study, there were no differences between groups in the volume of beer consumed. Schoenmakers and colleagues carried out a similar study where heavy social drinkers had learned to avoid alcohol-related stimuli and developed an attentional bias towards soft drinks, although training had no effect on craving or drink choice [32].

Only three laboratory studies have published findings on AR procedures in current tobacco smokers [26,30,31]. The first of these studies found that AR increased attentional bias in participants who were trained towards smoking-related stimuli and decreased attentional bias in those trained towards neutral stimuli [26]. Furthermore, when participants were measured on their response to a lit cigarette following the training procedure, greater increases in subjective craving were found in male participants who attended to smoking-related stimuli than those trained towards neutral stimuli. However, no effect of training on smoking topography (e.g. number of puffs taken, puff duration, etc.) was observed. In a replication of the study with a no-training control group, attentional bias was greater after training in the attend group than the avoid and no-training control groups, but these effects disappeared after 1 day [30]. Neither the train-to-attend or train-to-avoid manipulations had any effect on urge to smoke, although unlike in the previous study, no cue exposure task was used. No group effects of retraining on motivation to smoke were observed. McHugh and colleagues compared an avoid group with a no-training control group and found no change in attentional bias and no effects of retraining on subjective craving [31]. Unlike the two previous studies, no behavioural measures of tobacco-seeking were taken.

Collectively, laboratory studies of AR suggest that attentional bias can be modified and that, in some cases, corresponding changes in craving occur. While AR has not shown any effects on drug-taking behaviour in smokers, it is worth noting that laboratory studies of AR typically recruit samples of continuing smokers who are temporarily abstinent for the purpose of the experimental investigation. These smokers presumably have no motivation or intention to reduce their substance use in comparison to treatment-seeking smokers. Studies of AR in clinical populations are capable of addressing how attentional bias relates to real-world behaviour – particularly relapse - in addition to assessing the efficacy of AR as a clinical intervention.

Only two studies to date have examined the effects of AR in substance users seeking to reduce or abstain from drug use [27,33]. In an uncontrolled trial of AR, hazardous and harmful drinkers interested in reducing their alcohol intake completed 2 or 4 weekly sessions of AR on a modified Stroop task, respectively [27]. After treatment was complete, processing biases towards alcohol-related stimuli reduced in both groups, as did alcohol consumption by approximately 10 Units/week (1 Unit is equivalent to 8 g of ethanol) for the harmful drinkers. These reductions were also maintained at the 3 month follow up. Uncontrolled trials in people seeking to change their behaviour are difficult to interpret, however. In the only randomised controlled trial of AR in substance users, Schoenmakers and colleagues found that alcohol-dependent patients were more able to disengage attention from alcohol-related stimuli than control patients after 5 sessions of AR on a modified visual probe task, given in addition to standard treatment [33]. Moreover, relapse was delayed by over a month in patients that received AR. While there appear to be promising effects of AR as a clinical intervention in alcohol abusers, little is known about the clinical value of AR procedures in smokers attempting to quit.

